**5.0 Interventions**
5.1 **Preoperative preparation:** The basic condition of the patient was fully assessed before surgery, and preoperative examinations were completed to exclude surgical contraindications. The patient was informed of the condition and the risks related to the surgery, and a surgical informed consent form was signed.

5.2 **Surgical procedure:** All patients underwent the McDonald cervical cerclage procedure performed by the same experienced chief gynecologist and obstetrician, using Johnson & Johnson RS22 suture material. During the surgery, the cervix was fully exposed, and several oval forceps were used simultaneously to pull the cervix outward to retract the cervical os. If the amniotic sac protruded beyond the external cervical os, it was reduced to the level of the internal cervical os. In the one-stitch group, the Johnson & Johnson RS22 suture was used to perform a circular continuous suture and knot at the level of the cervicovaginal junction. In the two-stitch group, the first cerclage suture was performed in the same manner as the one-stitch group, and the second suture was performed again in a circular suture near the external cervical os below the first suture to close the external cervical os.

5.3 **Postoperative management:** Patients were placed in a Trendelenburg position for bed rest after surgery. Perioperative antibiotics were used to prevent infection, and external genital hygiene was maintained. Infection indicators, uterine contractions, vaginal discharge, and subjective symptoms of the patient were closely monitored. The changes in the cervix were dynamically monitored by ultrasound. Appropriate tocolytic agents were used according to gestational age and uterine contraction symptoms. The cervical cerclage was usually removed at 36-37 weeks of gestation. In case of definite signs of infection, preterm premature rupture of membranes (PPROM), inevitable miscarriage or preterm labor unresponsive to tocolytic agents, the cerclage should be urgently removed in the emergency department. The timing of cerclage removal should be grasped to reduce the occurrence of cervical laceration.

**6.0 Outcomes**
6.1 **Primary Outcome:** Spontaneous preterm birth at <34+0 weeks gestation.
6.2 **Secondary Outcomes:** As listed in section 2.2. Gestational dating was standardized using first-trimester crown-rump length (CRL) measurements (11-13 weeks). When discrepancy >7 days existed between last menstrual period (LMP) and ultrasound dating, CRL-based dating was prioritized.

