**7.0 Sample Size Calculation**

Based on historical data[1], the expected incidence of PTB <34 weeks was 89.5% in the emergency one-stitch group and 42.1% in the emergency two-stitch group. Assuming a power of 90% and a two-sided alpha of 0.05, a sample size of 44 patients was required for the emergency stratum. Accounting for a 5% dropout rate, a minimum of 46 patients per stratum (therapeutic and emergency) will be recruited, leading to a total target enrolment of 100 participants (50 per stratum, 25 per treatment arm within each stratum).

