**8.2 Blinding**

Due to the procedural nature of the intervention, the operating surgeons could not be blinded to the group assignment. However, the following blinding procedures were implemented:

Participants and Postoperative Nursing Staff: Were blinded to group assignment. This was achieved through standardised postoperative care protocols and by omitting documentation of the number of sutures in the patient's accessible medical records.

Outcome Assessors: Were blinded to the treatment allocation. The primary outcome (spontaneous preterm birth at <34 weeks) was determined based on objective criteria not subject to interpretation based on the surgical technique.

Furthermore, the researcher who managed the randomisation information did not participate in any subsequent trial stages. Although unblinded, surgeons were mandated to follow standardised operative checklists and were excluded from outcome evaluations.

This design ensured that potential confounding from clinical indication type was controlled through stratification, while preserving the properties of random allocation within each prognostic subgroup.

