**10.6 Subgroup and Other Analyses**

The primary analysis is stratified by indication (Therapeutic vs. Emergency), which serves as a pre-specified subgroup analysis.

No other subgroup or sensitivity analyses were pre-specified in the statistical analysis plan for this initial trial.

No interim analyses for efficacy or futility were planned or conducted.

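### The binary primary analysis has no usable rule for medically indicated births before 34 weeks, spontaneous is undefined, and it is unclear whether the planning rates refer to the same event

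*Protocol*

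**What the plan says.** Section 6.1 gives the primary outcome as "Spontaneous preterm birth at <34+0 weeks gestation"; sections 2.1 and 10.4.1 agree. No section says what makes a birth spontaneous. Section 10.4.1 treats the outcome as dichotomous, compared within each stratum by chi-square or Fisher's exact test, and 10.1 keeps every randomised woman in her allocated group.

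Medically indicated preterm delivery appears in two other places. Section 4.2(d) lists it among the exclusion criteria. Section 10.5 censors it in the Kaplan-Meier analysis.

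Section 5.3 lists the events that lead to urgent removal of the stitch: "In case of definite signs of infection, preterm premature rupture of membranes (PPROM), inevitable miscarriage or preterm labor unresponsive to tocolytic agents". It does not say how the birth that follows is to be classified. Section 8.2 states: "The primary outcome (spontaneous preterm birth at <34 weeks) was determined based on objective criteria not subject to interpretation based on the surgical technique". The criteria are not given.

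Section 7.0 plans on rates described this way: "the expected incidence of PTB <34 weeks was 89.5% in the emergency one-stitch group and 42.1% in the emergency two-stitch group". The word spontaneous is absent there. Section 10.6 adds, apart from the split by indication: "No other subgroup or sensitivity analyses were pre-specified".

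**The concern.** A birth before 34 weeks that is classed as indicated is not a spontaneous preterm birth. In a yes/no analysis of all randomised women it therefore falls in the same cell as a term delivery. The imputation rule in 10.2 does not catch it, because the outcome is known, not missing. Applying 4.2(d) instead would remove the woman because of something that happened after randomisation, which contradicts 10.1. Section 10.5 applies a third treatment, censoring. The same birth is thus a non-event, an exclusion or a censored observation, depending on the section.

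This matters more here than in many trials. Section 1.0 proposes that the second stitch works partly by restoring the mucus plug barrier and reducing ascending infection. Births that follow infection or membrane rupture therefore lie on the hypothesised treatment pathway, and their number may differ by arm. If some are labelled indicated, treatment failures could be scored as successes, unequally between arms, and no pre-specified analysis of the primary outcome would reveal it. Separately, if the planning rates describe a wider event than the one analysed, the stated power does not apply to the primary outcome.

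**Working it through.** **1. Inputs.** From section 7.0: rates p1 = 0.895 (one stitch) and p2 = 0.421 (two stitches); "Assuming a power of 90% and a two-sided alpha of 0.05, a sample size of 44 patients was required for the emergency stratum"; 25 per arm per stratum recruited. From 10.3 and 10.4.1: chi-square if all expected counts are at least 5, otherwise Fisher's exact test. Not in the document: the share q of births before 34 weeks that are medically indicated. It is assumed below.

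**2. The plan's own figure.** Without continuity correction, with mean rate 0.658:

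n per arm = [1.960·√(2·0.658·0.342) + 1.282·√(0.895·0.105 + 0.421·0.579)]² / 0.474² = (1.315 + 0.745)² / 0.2247 ≈ 18.9, so 19 per arm (38 in total).

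With continuity correction: (18.9/4)·[1 + √(1 + 4/(18.9·0.474))]² ≈ 22.9, so 23 per arm (46 in total). Exact power of Fisher's test at 22 per arm is 89.8%. The stated 44 is therefore sound for its own rates. Dropout: 44/0.95 = 46.3, stated as 46 and then raised to 50.

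**3. Power if the rates cover all births and indicated births count as non-events.** The primary event rates become p1(1 − q) and p2(1 − q). Power is the sum of binomial probabilities over all tables that the planned rule rejects:

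| q (assumed, same in both arms) | one stitch | two stitches | power, 22 per arm | power, 25 per arm |
|---|---|---|---|---|
| 0% | 0.895 | 0.421 | 94.2% | 97.0% |
| 10% | 0.806 | 0.379 | 84.3% | 90.7% |
| 20% | 0.716 | 0.337 | 73.1% | 82.0% |

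If Fisher's test were used throughout, the figures at 25 per arm would be 93.6%, 84.5% and 73.2%.

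**4. Power if such births are removed, as 4.2(d) would imply.** The rates become p(1 − q)/(1 − pq) and the arms shrink to 25(1 − pq). For q = 20%: 0.716/0.821 = 0.872 in 20.5 women against 0.337/0.916 = 0.368 in 22.9 women. Large-sample chi-square power is 96.2%, 95.6% and 94.8% for q of 10%, 20% and 30%. Power is then not the problem; departure from intention to treat is.

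**5. Possible bias.** Suppose the risk of any birth before 34 weeks is 60% in both arms, and the indicated share is 10% with one stitch and 30% with two. Spontaneous births are then 0.60·0.90 = 54% and 0.60·0.70 = 42%, so RR = 0.42/0.54 = 0.78 with no difference in births before 34 weeks. The chance of p < 0.05 at 25 per arm under the planned rule is about 16%. All three inputs are chosen for illustration.

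**The case against.** Spontaneous preterm birth is a legitimate, mechanism-specific endpoint for cerclage, and the plan has safeguards. Outcome assessors are blinded. Gestational age at delivery and latency are compared by arm without restriction to spontaneous births, so a shift from spontaneous to indicated births would tend to show there. Membrane rupture and chorioamnionitis are compared as well. These points stand, but they do not settle how an indicated birth enters the primary comparison.

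Several stronger readings are tempting and go beyond the text:

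- A reader might infer that births after infection or membrane rupture are counted as successes. No section says so. Section 5.3 speaks only of removing the stitch, and two of its four triggers (inevitable miscarriage and unresponsive preterm labour) are themselves spontaneous processes. The protocol permits such a classification by leaving the term open; it does not prescribe it.
- A reader might infer that the sample size uses all preterm births. Section 10.4.2 writes PTB for outcomes that 2.2 lists as spontaneous, so in 7.0 it may also be shorthand. Only the cited historical study could settle this.
- A reader might infer that the emergency stratum is underpowered. Under the planned rule, power at 25 per arm still exceeds 90% with a 10% indicated share, and no share is documented.
- A reader might take 10.6 as a ban on sensitivity analyses, or 8.2 as a claim that the outcome needs no judgement at all. Section 10.6 says only that none was pre-specified, and 8.2 claims only that surgical technique does not affect interpretation.

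**Conclusion.** The concern holds as a defect of definition and consistency. Sections 4.2(d), 10.1 with 10.4.1, and 10.5 give three incompatible treatments of the same post-randomisation event. The term that decides whether a birth is a primary event is undefined, and no pre-specified sensitivity analysis tests the choice.

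The effect on power is conditional. It arises only if the planning rates cover all births and indicated births are scored as non-events. With equal shares in both arms, emergency power at 25 per arm then runs from 97.0% (0%) through 90.7% (10%) to 82.0% (20%). If the rates already refer to spontaneous births, the planned size is adequate for them. The RR of 0.78 shows that bias is possible, not that it is likely or of that size. The point should be put right, but it does not show that the trial is underpowered or that failures will be miscounted.

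**What to change.** 1. In 6.1, define the primary event to include births before 34+0 weeks that follow PPROM, chorioamnionitis, preterm labour or cerclage removal for the reasons listed in 5.3, classified by the blinded assessors.
2. Remove 4.2(d) as a post-randomisation exclusion. State one rule for the remaining indicated births, and make 4.2, 10.1, 10.4.1 and 10.5 consistent with it.
3. In 10.6, pre-specify all births before 34+0 weeks, in all randomised women, as a sensitivity analysis of the primary outcome. It should inform interpretation; making superiority depend on agreement of both analyses would add a debatable second success criterion and is not needed.
4. In 7.0, state which event the 89.5% and 42.1% describe. If they cover all births, restate the power for the primary outcome.

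The cost is revised wording, one extra analysis of data already collected, and possibly a slightly lower stated power.

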**7.0 Sample Size Calculation**

Based on historical data[1], the expected incidence of PTB <34 weeks was 89.5% in the emergency one-stitch group and 42.1% in the emergency two-stitch group. Assuming a power of 90% and a two-sided alpha of 0.05, a sample size of 44 patients was required for the emergency stratum. Accounting for a 5% dropout rate, a minimum of 46 patients per stratum (therapeutic and emergency) will be recruited, leading to a total target enrolment of 100 participants (50 per stratum, 25 per treatment arm within each stratum).

**8.0 Randomisation and Blinding**
**8.1 Randomisation**

Participants were primarily stratified by clinical indication (Therapeutic cerclage cohort vs. Emergency cerclage cohort, n=50 per stratum). Within each stratum, they were randomly assigned (1:1) to receive either the one-stitch or two-stitch technique (n=25 per group) using a computer-generated random number sequence (created with SPSS 26.0) with permuted blocks of sizes 4 and 6.

Allocation concealment was implemented using sequentially numbered, opaque, sealed envelopes. For each eligible participant, an independent research nurse provided the corresponding envelope directly in the operating room. The envelope was opened by the surgeon only after anaesthesia preparation and the final decision to proceed with surgery. The surgeon had no access to the master allocation sequence, and only one envelope was present in the operating room at any time. Stratum-specific randomisation lists were maintained independently to prevent cross-stratum contamination.

**8.2 Blinding**

Due to the procedural nature of the intervention, the operating surgeons could not be blinded to the group assignment. However, the following blinding procedures were implemented:

Participants and Postoperative Nursing Staff: Were blinded to group assignment. This was achieved through standardised postoperative care protocols and by omitting documentation of the number of sutures in the patient's accessible medical records.

Outcome Assessors: Were blinded to the treatment allocation. The primary outcome (spontaneous preterm birth at <34 weeks) was determined based on objective criteria not subject to interpretation based on the surgical technique.

Furthermore, the researcher who managed the randomisation information did not participate in any subsequent trial stages. Although unblinded, surgeons were mandated to follow standardised operative checklists and were excluded from outcome evaluations.

This design ensured that potential confounding from clinical indication type was controlled through stratification, while preserving the properties of random allocation within each prognostic subgroup.

**9.0 Data Collection and Management**

Data will be collected prospectively using standardised case report forms (CRFs) and entered into a secure electronic database. All patient identifiers will be removed. Data quality will be ensured through regular audits and validation checks.

**10.0 Statistical Analysis Plan**

**10.1 Analysis Principles**

The primary analysis will be performed according to the intention-to-treat (ITT) principle, including all randomly assigned participants in the groups to which they were originally allocated.

A supporting per-protocol (PP) analysis will also be conducted, which excludes participants who did not receive the allocated intervention or who had major protocol violations.

A two-sided p-value of less than 0.05 will be considered statistically significant for the primary outcome. All analyses will be performed using SPSS software (version 26.0, IBM SPSS, Inc, Armonk, NY).

**10.2 Handling of Missing Data**

For the primary and secondary outcome, if data are missing, a conservative approach will be applied by imputing the missing participants as having experienced the event in the primary ITT analysis.

The PP analysis will simply exclude participants with missing primary outcome data.

**10.3 Analysis of Baseline Characteristics**

Baseline maternal demographics and clinical characteristics will be summarized by treatment group within each stratum (Therapeutic and Emergency).

Continuous variables will be assessed for normality using the Shapiro-Wilk test.

Normally distributed data will be presented as mean ± standard deviation (SD) and compared between groups using Independent Samples t-tests.

Non-normally distributed data will be expressed as median (Q1, Q3) and compared using the Wilcoxon rank-sum test (Mann-Whitney U test).

Categorical variables will be presented as number (percentage) and compared using:

Chi-square (χ²) test when all expected frequencies are ≥5.

Fisher's exact test when any expected frequency is <5.

**10.4 Analysis of Outcomes**

10.4.1 Primary Outcome

The primary outcome, spontaneous PTB <34 weeks, is a dichotomous variable.

It will be compared between the two-stitch and one-stitch groups within each stratum using a Chi-square test or Fisher's exact test as appropriate.

The relative risk (RR) with a 95% confidence interval (CI) will be calculated as the primary measure of effect size.

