**4.0 Participants, Inclusion and Exclusion Criteria**
4.1 **Inclusion Criteria (must meet one category):**
**Therapeutic Cerclage Cohort:** Singleton pregnancy at 16-28 weeks gestation with:
(a) History of spontaneous PTB <34 weeks AND current cervical length (CL) ≤25 mm at 16-28 weeks; OR
(b) No prior PTB BUT documented progressive cervical shortening with CL ≤25 mm at 16-28 weeks
**Emergency Cerclage Cohort:** Singleton pregnancy at 16-28 weeks gestation with painless cervical dilatation, with or without membrane prolapse.
4.2 **Exclusion Criteria:**
(a) Transabdominal cerclage;

(b) Using a pessary for cervical shortening;

(c) Fetal anomalies;

(d) Medically indicated preterm delivery;

(e) Lost to follow-up or incomplete documentation of delivery outcomes.

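### The primary RR in each stratum is crude, although one recorded-at-entry risk factor per stratum (membrane prolapse; preterm-birth history) is balanced only by chance at 25 per arm

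*Protocol*

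**What the plan says.** Protocol 10.4.1 fixes the primary analysis of spontaneous preterm birth before 34 weeks: "It will be compared between the two-stitch and one-stitch groups within each stratum using a Chi-square test" or Fisher's exact test, with an RR and 95% CI as the effect measure. No covariate is named. Section 10.4.2 applies the same crude methods to the secondary outcomes, 10.5 uses Kaplan-Meier curves and the log-rank test, and 10.6 states that no further subgroup or sensitivity analyses were pre-specified.

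Section 10.3 summarises baseline characteristics by arm within stratum and tests the arms against each other; normally distributed variables, for example, are "compared between groups using Independent Samples t-tests".

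Randomisation (8.1) is stratified by indication only, with "50 per stratum, 25 per treatment arm within each stratum". Within each stratum, section 4.1 admits two kinds of patient. The emergency cohort has "painless cervical dilatation, with or without membrane prolapse". The therapeutic cohort takes women with an earlier spontaneous preterm birth and a short cervix (category a), or women with "No prior PTB BUT documented progressive cervical shortening" (category b).

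**The concern.** Both entry factors are known before allocation and could plausibly bear on the risk of early delivery. Neither is balanced by design, and at 25 per arm sizeable differences are not rare. When one occurs, the crude RR reflects case mix as well as technique.

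The plan's only response is a significance test on the baseline table. Under concealed random allocation, any baseline difference is due to chance, so that test answers no useful question and corrects nothing. A small baseline p-value would invite an argument about adjustment after the results are known. Section 8.2 justifies stratification as control of confounding by indication; the same reasoning applies to these factors inside each stratum, and the plan does not carry it further.

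This is not a gap that a separate analysis plan would fill. Section 10 is itself titled as the statistical analysis plan, chooses the crude test and closes the list of other analyses.

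**Working it through.** **1. The plan's own sample size.** Inputs from section 7.0: "89.5% in the emergency one-stitch group and 42.1% in the emergency two-stitch group", 90% power, two-sided alpha 0.05, stated total 44.
- Pooled formula, n per arm = [1.96·√(2p̄q̄) + 1.2816·√(p₁q₁ + p₂q₂)]² / d², with p̄ = 0.658 and d = 0.474: (1.315 + 0.745)² / 0.2247 = 18.9, so 19 per arm, 38 in total.
- With continuity correction: 23 per arm, 46 in total.
- Exact power of Fisher's test at 22 per arm: 0.898.

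So 44 is consistent with Fisher's test at about 90% power. Dropout: 44/0.95 = 46.3, which rounds up to 47 against the stated 46. The planned RR is 0.421/0.895 = 0.47.

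**2. How often the arms differ.** The protocol gives no prevalence for either factor, so a range is shown. Chance of a difference of at least 20 points (5 women) at 25 versus 25:
- Number with the factor random (two independent binomials): 11% at prevalence 20%, 20% at prevalence 50%.
- Number in the stratum fixed (hypergeometric): 7%, 22%, 15% and 26% at prevalences 20%, 30%, 40% and 50%. The sequence is not monotone because counts are discrete.

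**3. What a 20-point imbalance does with no treatment effect.** Arm risk = prevalence × risk with factor + (1 − prevalence) × risk without. With 40% against 60% carrying the factor (all risks assumed):
- Risks 0.5 without, 0.7 with: 0.58/0.62 = 0.94
- Risks 0.5 and 0.9: 0.66/0.74 = 0.89
- Risks 0.3 and 0.7: 0.46/0.54 = 0.85

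**4. The same imbalance at the planned emergency rates.** Assumed risks without/with the factor, chosen to average to the planned rates at 50% prevalence: one-stitch 0.84/0.95, two-stitch 0.30/0.54.
- Imbalance favouring two-stitch: (0.6×0.30 + 0.4×0.54)/(0.4×0.84 + 0.6×0.95) = 0.396/0.906 = 0.44
- Imbalance against it: (0.4×0.30 + 0.6×0.54)/(0.6×0.84 + 0.4×0.95) = 0.444/0.884 = 0.50

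**5. Crude against adjusted, by simulation.** Pearson chi-square without correction against Cochran-Mantel-Haenszel (CMH), 25 per arm, 50% prevalence; the event rates and gradients are assumptions.
- Null, 60% in both arms, given an imbalance of at least 20 points in favour of two-stitch: false claims of benefit about 8% (30-point gradient) or 10.5% (40-point) crude, about 2.5% with CMH. Over all null trials the crude figure is 3.0%.
- SD of log RR in that null: 0.241 crude, 0.232 (30-point) or 0.222 (40-point) adjusted. Variance ratios: (0.232/0.241)² = 0.93 and (0.222/0.241)² = 0.85.
- Power at 70% versus 40%: 62% crude; CMH about 65% (40-point gradient), 61% (30-point) and 57% (no gradient).
- Power in the step 4 scenario: 97.0% crude, 97.2% CMH.

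**The case against.** The strongest case for leaving the plan alone has five parts.

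- **An unadjusted test is a valid primary analysis of a randomised trial.** Chance imbalance is part of the sampling error that the CI already carries. This stands. A reader might infer that the crude RR is biased or that type I error is broken by case mix; the documents do not support that. In simulation the crude test does have size near 6% against 5% for CMH, but the same 6.0% against 5.0% appears when the factor has no prognostic value. The gap comes from the uncorrected chi-square at this sample size.
- **The 8 to 10.5% false-claim rate selects unfavourable trials.** An imbalance that large in that direction occurs in about 10% of trials at 50% prevalence, so these claims amount to roughly 1% of all null trials. This stands, and the figure should be read as conditional.
- **The planned emergency conclusion is not threatened.** This also stands. With 89.5% in the one-stitch arm and 50% prevalence, the largest possible gradient there is 21 points (100% against 79%), so a 30 to 40-point gradient cannot occur at the planning rates. It could occur only if event rates were lower than planned, or in the therapeutic stratum, for which section 7.0 states no rate.
- **Baseline data are not wholly ignored.** Correct: indication is a baseline factor and structures both randomisation and analysis. The point concerns what lies beyond indication.
- **Changing the primary estimate may be too late.** Sections 10.5 and 10.6 are partly in the past tense. If outcomes by arm are known, replacing the primary estimate would itself be post hoc. The fix allows for this.

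**Conclusion.** The point holds in a limited form and is a worthwhile improvement, not the correction of an invalid analysis. Beyond indication, nothing in the plan protects the primary RR against a chance imbalance in the one entry factor that its own eligibility criteria distinguish within each stratum, and the baseline tests do not supply that protection.

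The size depends on prevalence and prognostic strength, neither of which the protocol gives. Under the assumptions shown, a 20-point imbalance has a chance of about 7 to 26%. It shifts a null RR by 6 to 15%, and adjustment removes that shift. The precision gain is modest: about 7 to 15% in the variance of the log RR with a 30 to 40-point gradient, and none if the factor is not prognostic. At the planned emergency effect the shift is small (0.47 to 0.44 or 0.50). It matters more if the true effect is smaller than planned.

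**What to change.** - **10.4.1:** in each stratum, pre-specify a Mantel-Haenszel RR with 95% CI and the CMH test over one binary factor: membrane prolapse (yes/no) in the emergency cohort, entry category (a)/(b) in the therapeutic cohort. Report the crude RR beside it. State whether the CMH test uses a continuity correction. With 25 per arm, keep to this single factor.
- **Timing:** make the adjusted RR primary only if the change is documented before outcomes are examined by arm. If they are already known, keep the crude RR primary and label the adjusted RR as supporting.
- **10.3:** describe baseline characteristics by arm within stratum, without p-values.
- **Data:** confirm that the case report form records prolapse at entry as a defined item; the protocol does not show this. Entry category follows from eligibility.

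**Cost:** a few lines of text, and no extra patients or visits. The statistical price is little or no gain if the factor is not prognostic, and some loss of nominal power against the uncorrected chi-square. At 70% versus 40% this is about 1 point with a 30-point gradient and up to about 6 points with no gradient (62% to 57% after rounding). Part of that loss only reflects the chi-square test's size of about 6% rather than 5%.
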